#### 2.6.3. Triangulation of Data

The totality of the quantitative and qualitative data will be triangulated and interpreted together. We anticipate that the quantitative data will mainly provide insights into how people engaged with the intervention, whereas the qualitative data will provide insights into why they felt/acted this way. We will systematically compare and integrate the findings to assess where they converge or diverge. This will enable a more robust and holistic understanding of the Flourishing Intervention tools and inform further refinements to proceed to the next phase of an effectiveness trial. If the data sets are divergent, and depending on the extent of the divergence, the research team will undertake several strategies to address the divergence, including (a) reconciliation—a re-review of the raw data; (b) bracketing—acknowledging the conflict and/or separating the analyses and contextualising; and (c) complementary explanation—using the divergence to explain the complexity of a phenomenon. Furthermore, engagement metrics will also provide a more objective snapshot of Pathway Tool use if divergent findings are reported between the qualitative and quantitative datasets. For a visual summary of data triangulation, see Figure 3.

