## 2. Materials and Methods

### 2.1. Study Design

A randomised feasibility trial will be used to test the feasibility and acceptability of a new flourishing intervention and explore any areas for modification required (primary aim). A secondary aim will be to explore whether the intervention group shows any improvements in parent outcomes relative to controls after engaging with the Pathway Tool. This protocol is reported in accordance with SPIRIT guidelines and informed by the CONSORT extension for pilot and feasibility trials (see Section S2 of the Supplementary Materials) [40].

Participants will complete a screening form to determine eligibility and then be randomly allocated to either the intervention group (which will gain access the Pathway Tool immediately after completing the Flourishing Check), or the waitlist-control group (which will continue their usual activities and only gain access to the Pathway Tool after post-test assessments are completed or the final data collection time point has closed).

Quantitative and qualitative data will be collected at five timepoints: [T1] pre-intervention (baseline); [T2] acceptability and feasibility questionnaires (intervention group only), 1 week after T1; [T3] test–retest reliability (n = 200), 2–4 weeks after T1; [T4] qualitative feedback on the Flourishing Check and Pathway Tool (*n* ≈ 30, intervention group only), 3 months after T1; and [T5] post-intervention outcome measures, 6 months after T1. See Table 1 for a summary of the research procedure.

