### 2.6. Data Analysis

#### 2.6.1. Primary Outcomes

Acceptability and Feasibility:

The acceptability and feasibility of the Flourishing Check and Pathway Tool will be assessed using a convergent mixed-methods design [52] involving data from questionnaires and focus groups. Additional themes emerging from focus groups, as well as website engagement metrics, will inform future modifications to these tools. Convergent or concurrent mixed methods (also called “parallel”) projects gather quantitative and qualitative data separately, or parallel to each other, and analyse them together. All quantitative and qualitative data will be triangulated and compared for consistency, validity, and credibility. The results will be synthesised to identify themes and recommendations for improving the intervention. Table 3 provides a summary of the data triangulation process and criteria to meet different levels of feasibility and acceptability. This has been created based on the ADePT framework, where 3 categories (green, amber, or red) are used to assess whether a study should progress from a pilot to an efficacy trial [53].

Questionnaires:

The author-developed questionnaires will assess the ease of use, understanding, visual appeal, acceptability of language, readability, functionality, and ease of navigation of the Flourishing Check and Pathway Tool, with higher scores operationalised as greater acceptance. These data will be analysed using descriptive statistics. Additionally, responses to open-ended questions will be subjected to thematic analysis according to best practice, described below [54].

Focus Groups:

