Focus groups will be used to assess the feasibility and acceptability of the Pathway Tool. Using the approach of Braun and Clarke [54] for thematic analysis, transcripts will be iteratively coded, and codes will be collated into higher-level themes. Transcripts will be reviewed to identify all instances of thematic codes, with codes expanded or collapsed as required. Qualitative data will be analysed using qualitative content analysis [55], assigning a code to each concept using NVivo 14. Similar concepts will be identified and categorised into categories. Data will be analysed using a phenomenological approach (i.e., as a description of experiences as consciously experienced by participants), and narrative themes will be deducted until saturation. The coding process will be guided by the following deductive constructs: intervention acceptability, engagement, and application; mental health and wellbeing experiences; and suggestions for programme revisions.

Engagement metrics:

This data will be used for exploratory purposes to understand how users interact with suggested resources. Exploratory engagement (e.g., clicking resources within the tool or following external links) will indicate whether recommendations are perceived as relevant and worth investigating, supporting acceptability. Recurring engagement, such as saving resources, will indicate sustained interest and practical feasibility of repeated use over time. Collaborative engagement (i.e., copying links to share with others) will further signal acceptability by indicating that users value the content enough to recommend it within their community. These metrics will inform future modifications to the Pathway Tool if the feasibility or acceptability receives an ‘amber’ outcome (see Table 3).

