Flourishing Check	<40% of participants rated all key acceptability items as ≥4 AND Focus groups revealed repeated themes of low to moderate acceptability	40–60% of participants rated all key acceptability items as ≥4 AND Focus groups revealed repeated themes of moderate to high acceptability	>60% of participants rated all key acceptability items as ≥4 AND Focus groups revealed repeated themes of high acceptability
Pathway Tool	<40% of participants rated all key acceptability items as ≥4 AND Focus groups revealed repeated themes of low to moderate acceptability	40–60% of participants rated all key acceptability items as ≥4 AND Focus groups revealed repeated themes of moderate to high acceptability	>60% of participants rated all key acceptability items as ≥4 AND Focus groups revealed repeated themes of high acceptability
Flourishing Check	<40% of participants rated all key feasibility items as ≥4 AND Focus groups revealed repeated themes of low to moderate feasibility	40–60% of participants rated all key feasibility items as ≥4 AND Focus groups revealed repeated themes of moderate to high feasibility	>60% of participants rated all key feasibility items as ≥4 AND Focus groups revealed repeated themes of high feasibility
Pathway Tool	<40% of participants rated all key feasibility items as ≥4 AND Focus groups revealed repeated themes of low to moderate feasibility	40–60% of participants rated all key feasibility items as ≥4 AND Focus groups revealed repeated themes of moderate to high feasibility	>60% of participants rated all key feasibility items as ≥4 AND Focus groups revealed repeated themes of high feasibility

Note: For each feasibility and acceptability outcome, analyses will be stratified by age group (0–2 years and 3–5 years). See Section S6 of the Supplementary Materials for further details of key acceptability and feasibility items.

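### Table 3's focus-group theme grade is not protected from knowledge of the questionnaire percentage, and four of nine percentage-by-grade combinations have no colour

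*Protocol article*

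**What the plan says.** **The rule.** Table 3 has four rows (acceptability and feasibility, each for the Flourishing Check and the Pathway Tool) and three colours. Every cell has the same two-part form. For acceptability:

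- Red: "<40% of participants rated all key acceptability items as ≥4 AND Focus groups revealed repeated themes of low to moderate acceptability"
- Amber: "40–60% of participants rated all key acceptability items as ≥4 AND Focus groups revealed repeated themes of moderate to high acceptability"
- Green: ">60% of participants rated all key acceptability items as ≥4 AND Focus groups revealed repeated themes of high acceptability"

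Green means going to a full-scale trial without refinement.

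**Timing.** Table 1 and Section 2.1 place the Check questionnaire at T1, the Tool questionnaire at T2 (one week later) and the focus groups at T4 (three months after T1).

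**Analysis.** Section 2.6.1 describes a convergent design, whose projects "gather quantitative and qualitative data separately, or parallel to each other, and analyse them together". On the focus groups it says: "The coding process will be guided by the following deductive constructs: intervention acceptability, engagement, and application; mental health and wellbeing experiences; and suggestions for programme" (the last item being suggested changes to the programme). Codes may be expanded or collapsed.

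**Divergence.** Section 2.6.3 has the research team choose among strategies, "including (a) reconciliation—a re-review of the raw data", then bracketing, then complementary explanation. For the Pathway Tool it adds engagement metrics as a more objective source. It does not say which strategy applies when, what happens to the theme grade, or what colour results.

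**The concern.** The percentage is a count against a fixed threshold. The theme grade is a judgement, and the article gives no cut-off for low, moderate or high; the note to Table 3 refers to Section S6 for the key items only. The judgement falls to the team that conceived the intervention (Section 1.4) and expects it to be acceptable and feasible (Sections 1.8 and 3).

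Two sources corroborate each other only if each is graded before they are compared. If the grade can be set, or revisited after disagreement, with the percentage known, agreement between them carries less weight. At stake is the primary aim and the decision on whether, and in what form, an effectiveness trial follows.

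**Working it through.** **1. The quantitative half.** The sample-size paragraph (Section 2.6.2) assumes 60%, a margin of ±5 points and 95% confidence:

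n = z² p(1 − p) / d² = 1.96² × 0.60 × 0.40 / 0.05² = 368.8, so 369.

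This reproduces the plan's figure. The half-width is 5.0 points at 369 and 4.8 points at 400. The percentage therefore has a definition and a stated precision.

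**2. What the grade can change.** Read the grades as three levels and cross them with the three percentage bands of Table 3:

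| Band | Low | Moderate | High |
|---|---|---|---|
| <40% | Red | Red | none |
| 40–60% | none | Amber | Amber |
| >60% | none | none | Green |

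Five of nine combinations have a colour, and in all five it is the colour of the percentage band. The other four (9 − 5 = 4) have none. The grade therefore confirms the band's colour or leaves the result undefined.

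**3. What a regrade would do in the four undefined combinations.**

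- <40% with high: one step down to moderate gives Red.
- 40–60% with low: one step up to moderate gives Amber.
- >60% with moderate: one step up to high gives Green.
- >60% with low: two steps up to high gives Green.

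In each case, with the percentage held fixed, the only colour a regrade can reach is the one the percentage already points to. For illustration, 62% with moderate themes has no colour. If re-review finds "Focus groups revealed repeated themes of high acceptability", the same ratings give Green.

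**4. Whether the percentages could be known first.** Assume that T1 follows enrolment directly and that recruitment takes the planned three months (Section 2.2.1).

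- Last T2 due: 3 months + 1 week, about month 3.25.
- Last T2 closed: Section 2.2.2 sets T2 reminders at 7 and 14 days. Section 2.2 marks records incomplete two weeks after the second reminder, and the reminders it describes (for T5) come at one and three weeks. Closure is thus 4 to 5 weeks after the due date, or 3 months + 5 to 6 weeks, about month 4.2 to 4.4.
- T4 window: month 3 (first participant) to month 6 (last).

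Most ratings would exist by the time focus-group transcripts are graded. The article does not say when they are tabulated.

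**5. Feasibility.** Section 2.6.1 says the focus groups assess the feasibility and acceptability of the Pathway Tool. Two of the four Table 3 rows require a graded feasibility theme. The listed constructs name acceptability but not feasibility.

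**The case against.** **The design integrates the strands on purpose.** A convergent design brings them together, and Section 2.6.3 gives them different roles: how people engaged, and why. No text says the qualitative half is meant as an independent check. This stands as a description of the design. It does not prevent grading first and integrating afterwards.

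**Re-review is only one strategy.** Bracketing and complementary explanation keep a conflict visible, and engagement metrics offer another source for the Tool. This stands too. But no text says which strategy applies or what colour follows. The metrics cover the Tool only, and Section 4.1.2 says unverified users may inflate them.

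**The text does not say that a grade is revised.** Correct: it refers to the raw data without naming a strand. Data screening under Section 2.5 could also change which questionnaire records count, so it cannot be said that only the grade can move.

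**Collected is not the same as known.** Section 2.4 plans no interim analysis, and nothing says the percentages are tabulated before the themes are graded.

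**The article is condensed.** Coding workflow and masking may be set out in the full protocol, the supplement or Figure 3, which are not shown. The analysis plan for the Check questionnaire, which supplies the percentage in two rows, is deferred to a separate paper (footnote to Table 1). Silence on masking alone would therefore be no finding. The point rests on what the article does state: the two-part rule with its undefined combinations, and a divergence procedure with no stated outcome.

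**Feasibility may be covered indirectly.** Engagement, application and suggested revisions bear on it, and codes may be expanded. That softens the omission, but two decision rows still have no named construct.

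**Conclusion.** The point holds in a limited form. As stated, the plan does not protect the theme grade from knowledge of the percentage, and it gives no colour to 4 of 9 combinations in each of the four rows. The combination that matters most is more than 60% with moderate themes, where one step of regrading separates an undefined result from Green.

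Three stronger readings are not supported:

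- *The grade decides the colour.* It does not. Every defined colour follows the percentage band, and no regrade at a fixed percentage moves a result from one colour to another.
- *The two halves are dependent.* The documents leave this possible; they do not show it.
- *Any pull favours the team's hypothesis.* The pull is towards the percentage. It favours the hypothesis when ratings are high, but with under 40% and high themes it leads to Red.

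The count of four assumes three separate grades. If the table's three phrases are themselves the categories, only the three matching pairs have a colour and six of nine do not (9 − 3 = 6). The conclusion is the same. The timing rests on the assumptions given with it. This is a cheap improvement to a go/no-go rule, not an error in a computed figure.

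**What to change.** In Sections 2.6.1 and 2.6.3, and in Table 3 where needed:

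1. Assign, date and lock each theme grade before the T1 and T2 acceptability and feasibility percentages are tabulated.
2. Use the locked grade for the colour. Reconciliation may explain a divergence but does not replace the grade. Report any reconciled grade alongside it.
3. Give each of the four discordant combinations a colour in advance, for example the less favourable of the two implied. Locking alone is not enough: a locked moderate beside 62% still has no colour. Because moderate appears under both Red and Amber, the rule must name the colour for more than 60% with moderate themes explicitly.
4. Add feasibility as a deductive construct, so that the two feasibility rows have their own coded evidence.

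The cost is protocol wording and the order of work. Tabulation waits some weeks until the grades are locked. No further data or staff are needed.

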### 2.7. Dissemination of Results

The results of this study will be disseminated through peer-reviewed publications, presentations at national and international conferences, and plain language summaries sent to participants who opt to receive information about study outcomes. Findings will be circulated transparently regardless of the direction and significance of results.

## 3. Expected Results

We hypothesise that the Flourishing Intervention (Flourishing Check and Pathway Tool) will be acceptable and feasible to parents of children aged 0–5 years, as indicated by questionnaire responses and qualitative feedback (primary aim). Given the brief duration of the intervention and follow-up period, and the relative stability of many parenting and wellbeing characteristics over short timeframes, we anticipate detecting only small changes in most of the secondary outcome variables. We do not anticipate that we will detect significant improvements to parental wellbeing or paediatric quality of life within the timeframe of this study. However, this will be measured to assess the feasibility and sensitivity of these measures, and to inform effect size estimates and outcome selection for a future trial evaluating the intervention’s effectiveness.

## 4. Discussion

The protocol details a procedure to test the acceptability and feasibility of the Flourishing Intervention, a new digital intervention designed to promote early childhood and family flourishing. The primary aim is to assess whether the Flourishing Intervention is feasible and acceptable to parents and the secondary aims are to explore the potential efficacy of the intervention in improving (i) perceived self-efficacy in recognising and supporting flourishing in early childhood, (ii) perceived knowledge of how and when to seek support, (iii) engagement with and participation in supports relevant to flourishing in the early years, (iv) parental wellbeing, and (v) paediatric quality of life. It is hypothesised that the intervention in this pilot trial will be evaluated as feasible and acceptable based on the integration of qualitative and quantitative data.

This will be the first study to test the acceptability and feasibility of an early childhood flourishing assessment and digital intervention providing recommendations to local and national evidence-based supports. Parents are utilising online sources of information more frequently, but also report feeling overwhelmed by the volume of information available to them [56,57]. Online information comes from a wide variety of sources, increasing its potential to be conflicting and unreliable [58].

Parents need tools that reduce the burden of identifying the most appropriate support for their children [10]. The Flourishing Intervention has the potential to benefit parents and children by (1) reducing the time spent finding support, (2) improving parental awareness of their children’s strengths and support needs, and (3) promoting engagement with evidence-based programmes, services, and resources which promote flourishing.

Digital parenting interventions targeting early childhood aim to improve child and parent outcomes; however, many prioritise reducing child problem behaviours rather than enhancing strengths [16,19,24]. The Flourishing Intervention was developed through rigorous codesign with a range of primary and secondary stakeholders [10] and aims to promote flourishing by addressing problems and enhancing strengths.

Improving childhood health and wellbeing globally is a recognised imperative [1,2,3,4,5,6,7]. By increasing parents’ awareness of their children’s flourishing and knowledge of how to access support at a local level, this broader project (the feasibility and acceptability trial followed by an efficacy trial and scale-up) may inform methods for promoting early childhood flourishing at a larger scale.

### 4.1. Strengths and Limitations

#### 4.1.1. Strengths

There are multiple strengths to this protocol. A key strength of this methodology is its extensive and ongoing co-design with the community [10] and expert advisory groups. The resulting intervention is more likely to be engaging, acceptable, feasible, and meaningful to users [59].

A mixed-methods triangulation design will be utilised in the analyses. This approach was chosen as quantitative and qualitative methods can complement one another and together provide a more robust analysis [60]. By elevating parents’ voices through focus groups, this study will continue to engage in meaningful co-design with intended end-users and empower consumers [61]. The use of website metrics to track user engagement will allow for an in-depth understanding of how users engage with the Pathway Tool. This will allow the research team to improve the tool in future iterations.

#### 4.1.2. Limitations

There are limitations within this study that should be acknowledged. Participants will be self-selected from the Perth metropolitan area, with a focus on the Joondalup and Wanneroo regions. This may limit our ability to generalise conclusions about the acceptability and feasibility of the Flourishing Intervention beyond this area and to parents who are less likely to engage with digital tools. Additionally, all measures, barring engagement metrics, rely on self-report or parent proxy reports. Therefore, results may be distorted by biases or responder characteristics. Where possible, parenting outcome items included objective indicators (e.g., through questions about engagement with specific programmes) (see Section S3 of the Supplementary Materials for further details). While measurement of wellbeing in children under five years necessarily relies on parent reports [38], future research should incorporate objective measures and, where feasible, include the voice of the child. Additionally, participants will not be blinded to the condition they are allocated to, and those in the control condition may find a way to access the Pathway Tool (though this will be partly prevented by keeping the URL hidden from searches). If this occurs, this could potentially interfere with the engagement metrics recorded.

Lastly, the Consumer and Community Advisory Committee strongly agreed that enforcing user registration may create a barrier to engagement with online content. Therefore, participants will not have to create a user account to engage with the Pathway Tool. This limits our ability to control who accesses the tool, as anyone who receives the URL can access it. Therefore, engagement metrics may be inflated by users who are not verified, participants. Additionally, control participants may gain access to the tool during the study. This will be partly mitigated by the URL being hidden from searches. Given the low-risk nature of the intervention and the study context, more intensive monitoring approaches (e.g., individual-level tracking, mandatory logins, or detailed analytics linkage) were considered disproportionate to the aims of the study and not feasible within available resources. Importantly, such approaches would also introduce additional privacy considerations and participant burden, which may further impact participation and engagement. Future research could implement stricter controls to more accurately assess the efficacy of the Pathway Tool.

